**Supporting preliminary data.** We recently completed a small pilot study evaluating the initial efficacy of IBT. Waitlisted opioid-dependent adults were randomly assigned to an IBT (n=25) or Waitlist Control (WLC; n=25) condition, each 12 weeks in duration. IBT participants received BUP maintenance with bi-monthly visits to the clinic for staff-observed dose ingestion and the remaining doses dispensed at home via Med-O-Wheel. They also received IVR-generated nightly check-in calls as well as random call-backs. WLC participants remained on the waitlist of their local clinic. All participants completed 4-, 8- and 12-week follow-up assessments. Our primary outcome was the percent of participants in each group providing urine specimens that tested negative for illicit opioids at these monthly assessments.

**Participants randomized to receive IBT provided significantly more illicit opioid-negative urine specimens than those randomized to WLC at Weeks 4 (88% vs. 0%), 8 (84% vs. 0%), and 12 (68% vs. 0%) assessments ( $p$ 's<.001).** They also demonstrated greater reductions in past-month frequency of IV use ( $p$ <0.001). We also saw evidence of unexpected IBT-related benefits beyond abstinence, particularly in the area of psychological distress. IBT participants demonstrated greater reductions on the Beck Depression Inventory (BDI), with IBT participants reporting lower levels of depression at Weeks 4, 8, and 12 ( $p$ 's≤.01). A similar pattern was seen on the Addiction Severity Index (ASI) Psychiatric subscale ( $p$ =.02). These data suggest that IBT may produce improvements in psychological symptom severity among waitlisted opioid-dependent individuals, even without formal counseling.

Study retention was high among IBT and control participants (92% and 80%, respectively) and did not differ between groups ( $p$ =.42). IBT participants' adherence with the treatment components was also excellent. For example, participants took 99% of scheduled doses and completed 96% of daily calls, which averaged 1.24±0.4 minutes. They satisfied 96% of random call-backs, with 85% of specimens collected at those random visits negative for illicit opioids. The HIV+HCV application was associated with improvements in HIV- and HCV-related knowledge, and these improvements also persisted though 12-week follow-up. Finally, IBT participants' ratings of treatment satisfaction were high (4.6±0.7 on a 5-point scale).

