## METHODS AND PROCEDURES

**Study Design:** Describe the research design, including a description of any new methodology and its advantage over existing methodologies.

In this parallel-group randomized controlled trial (RCT), we will evaluate 6-month IBT efficacy in 100 waitlisted opioid-dependent adults. Participants randomly assigned to IBT (n=50) will receive (a) BUP maintenance with bi-monthly visits for observed medication ingestion and the remaining doses dispensed via Med-O-Wheel. (b) Daily monitoring calls via IVR, (c) IVR-generated random call-backs, and (d) HIV+Hepatitis C education via iPad. WLC participants will remain on the waitlist for their treatment of choice. Participants in both groups will complete monthly follow-up assessments. At all scheduled, random and follow-up assessment visits, urine specimens will be collected under staff observation and analyzed immediately for opioid and non-opioid drugs. We hypothesize that IBT participants will achieve significantly greater biochemically-verified illicit opioid abstinence relative to WLC. Secondary outcomes will include IV opioid and other drug use, psychosocial functioning (e.g., ASI subscales reflecting legal, employment, medical, psychiatric, drug and family/social severity), psychological distress (e.g., BDI, BAI, BSI) and several IBT-specific measures (e.g., BUP adherence, IVR utilization, patient satisfaction).

**Procedures:** Describe all procedures (sequentially) to which human participants will be subjected. Identify all procedures that are considered experimental and/or procedures performed exclusively for research purposes. Describe the types, frequency and duration of tests, study visits, interviews, questionnaires, etc. Include required screening procedures performed before enrollment and while on study. Please provide in table, list or outline format for ease of review. (describe and attach all instruments)

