**Withdrawal Procedures:** *Define the precise criteria for withdrawing subjects from the study. Include a description of study requirements for when a subject withdraws him or herself from the study (if applicable).*

Completing study visits and providing urine specimens as scheduled are necessary in order for subjects to receive the study medication. Thus, if the subject fails to attend scheduled visits, or does not submit regularly scheduled urine specimens, or if there is any evidence of nonadherence to the medication regimen, they will be withdrawn from the study. If they are discharged from the study, subjects will be expected to return all remaining medication and the Med-O-Wheel device to study staff immediately. Females will be tested for pregnancy prior to and during the study. Should a subject become pregnant during the trial, her participation will be terminated and she will be assisted with accessing treatment at the medical center's high-risk pregnancy clinic.

Patients are free not to participate in this study or to withdraw from it at any time. If they decide not to participate in the study, we will be glad to discuss with them other treatments that may be available in Vermont, including residential, outpatient, and medication-assisted treatment options. If patients decide not to participate or to withdraw from this study, their decision will not prejudice their future medical care at UVM or UVM Medical Center.

**Sources of Materials:** *Identify sources of research material obtained from individually identifiable human subjects in the form of specimens, records or data. Indicate whether the material or data will be obtained specifically for research purposes or whether use will be made of existing specimens, records or data.*

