Following stabilization, participants will visit the clinic every two weeks (i.e., Weeks 2, 4, 6, etc.) to provide a urine specimen, ingest that day's BUP dose under nurse observation, and complete measures of opioid and other drug use via Time-Line Followback. They will receive the doses for the upcoming interval in a Med-O-Wheel device (Addoz, Forssa, Finland) for ingestion at home. The Med-O-Wheel is a portable pill dispenser with tamper resistant features. Participants will be instructed to bring the device

with them to each study visit, as well as random call-backs (below) and reminded throughout the study that any evidence of nonadherence may be grounds for discharge. Participants can also return to the clinic between scheduled visits should any concerns arise or a dose evaluation be needed. Research staff will work with IBT participants throughout the trial to line up a provider for continued treatment in the community following the study. If a treatment slot is available, we will coordinate a smooth transfer to that program to begin the day following the Week 24 assessment.

**IVR daily monitoring.** The IVR system will contact participants each evening at a convenient time identified by them to assess opioids and other drug or alcohol use, as well as opioid craving and withdrawal. Instances of use, craving or withdrawal will prompt additional detailed questions (e.g., type and amount used, severity of craving and withdrawal), as well as provision of information about support meetings taking place in the community. Participants can make inbound calls to the system at any time to complete their daily check-in if they anticipate missing the call. They can also reach study staff at any time using our on-call mobile phone.

**Random call-backs via IVR.** Participants will be contacted via IVR approximately twice per month (once per two-week dosing interval) on a random basis and instructed to return to the clinic within 12 hours. For each random call-back, they will refrain from taking that day's dose and instead bring in their Med-O-Wheel device to ingest their medication under nurse observation. The research nurse will conduct a pill count and inspect the device for any evidence of tampering or nonadherence, and participants will provide breath and urine specimens (see Biochemical monitoring).

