**HIV+Hepatitis education.** Using an interactive iPad application developed by us, during Week 1 participants will complete a baseline assessment of HIV and hepatitis knowledge, including a modified version of the HIV/AIDS Knowledge Test (Marsch et al., 2005), a Hepatitis C knowledge test developed by our group, and VAS items assessing perceived risk, disease transmission and risk behaviors (Dunn et al., 2013). Upon completion of the pre-test, the application will provide immediate corrective feedback of any incorrect items (excluding VAS items) and an explanation of the correct answer. Participants will then view an interactive flipbook ("HIV/AIDS Basics", Aids.gov) and a brief video ("What is Hepatitis C and how is it diagnosed?", Foundation for AIDS Research), both delivered by iPad. They will complete a post-test assessment immediately following the educational module, and staff will offer condoms and information on free HIV and hepatitis testing in the community. The knowledge post-test will be repeated at Weeks 12 and 24.

**Overdose prevention.** We will evaluate the OD educational module in a manner similar to the HIV+Hepatitis Education above (i.e., pre-test, intervention, immediate post-test, follow-up post-tests at Weeks 12 and 24). Briefly, during Week 1, participants will complete a baseline assessment of opioid OD knowledge using the BOOK questionnaire (Dunn et al., 2016bc). Participants will then complete a brief (15-min) OD educational application via iPad, which consists of 28 slides that combine text, picture, and/or videos in the above content areas. The knowledge post-test will be repeated immediately following the intervention and at Weeks 12 and 24. We will also assess any instances of OD and naloxone use at each visit.

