### Statistical methods

IBT and WLC groups will be compared on baseline characteristics using analyses of variance for continuous and chi-square tests for categorical variables. If characteristics differ significantly and are predictive of outcome, they will be considered as covariates in subsequent analyses. The primary outcome

will be the percent of participants in IBT and WLC conditions with biochemically-confirmed illicit opioid abstinence at the 24-week assessment, evaluated based on a Cochran-Mantel-Haenszel (C-M-H) chi square test with site as the stratification variable. Primary analyses will include all randomized subjects independent of early dropout and with missing urine specimens considered positive for illicit opioids, consistent with an intent-to-treat approach (Armitage, 1983). The Breslow-Day test will be used to test homogeneity of the treatment effects across sites. If applicable, logistic regression will be used to adjust for baseline covariates confounded with treatment group. Though not the primary outcome, abstinence at other monthly assessments will be compared across treatments with Bonferroni-adjusted C-M-H tests to control experiment-wise type I error rate below  $\alpha=.05$ . Within the IBT group, generalized estimating equation (SAS, PROC GENMOD) will be used to characterize the temporal trend in abstinence across assessments. Fixed factors will include recruitment site and the within-subject factor, assessment time, along with their interactions. Repeated measures analyses of variance (SAS, PROC MIXED) will be used to compare groups on continuous outcomes (e.g., past-month frequency of illicit opioid and IV use, ASI subscales, BDI, HIV knowledge, OD risk knowledge). If significant treatment by time interactions are detected, partial F-tests will be used to examine simple effects of treatment at each assessment. Additional repeated measures analyses will characterize temporal patterns in IBT-specific outcomes (e.g., BUP adherence, IVR utilization, satisfaction). For WLC participants who after 24 weeks transition to IBT, estimates of abstinence will be obtained with corresponding 95% confidence intervals at each assessment. Statistical analyses will be performed using SAS V9.4 (SAS Institute, Cary, NC).

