**Adverse Event and Unanticipated Problem (UAP) Reporting:** Describe how events and UAPs will be evaluated and reported to the IRB. All protocols should specify that, in the absence of more stringent reporting requirements, the guidelines established in the Committees on Human Research "Adverse Event and Unanticipated Problems Reporting Policy" will be followed. The UVM/UVM Medical Center process for review of adverse events and UAPs to subjects or others should be included in the DSMP.

AEs and SAEs will be assessed at each clinic visit by a trained RA or nurse. Any SAE will be brought to the attention of the PI as soon as possible and not longer than 24 hrs. Any SAE, whether or not related to study intervention, will be reported to the IRB using the UVM Adverse Event Reporting Document within 5 days of the event. The IRB will make a determination as to whether additional reporting requirements are needed. Any SAEs will also be summarized in the yearly IRB continuing review, including a review of frequency and severity.

**Withdrawal Procedures:** Define the precise criteria for withdrawing subjects from the study. Include a description of study requirements for when a subject withdraws him or herself from the study (if applicable).

Completing study visits and providing urine specimens as scheduled are necessary in order for subjects to receive the study medication. Thus, if the subject fails to attend scheduled visits, or does not submit regularly scheduled urine specimens, or if there is any evidence of nonadherence to the medication regimen, they will be withdrawn from the study. If they are discharged from the study, subjects will be expected to return all remaining medication and the Med-O-Wheel device to study staff immediately. Females will be tested for pregnancy prior to and during the study. Should a subject become pregnant during the trial, her participation will be terminated and she will be assisted with accessing treatment at the medical center's high-risk pregnancy clinic. Patients are free not to participate in this study or to withdraw from it at any time. If they decide not to participate in the study, we will be glad to discuss with them other treatments that may be available in Vermont, including residential, outpatient, and medication-assisted treatment options. If patients decide not to participate or to withdraw from this study, their decision will not prejudice their future medical care at UVM or UVM Medical Center.

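### Discharge removes participants from the study while harms are sought only at visits, so SAEs, overdoses and deaths between discharge and Week 24 may go unrecorded, chiefly in IBT (both trials)

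*Supplement*

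**What the plan says.** The Supplement holds a Trial 1 and a Trial 2 protocol whose safety and withdrawal texts are almost the same.

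- **Finding events.** Under Adverse Event and Unanticipated Problem (UAP) Reporting, both say "AEs and SAEs will be assessed at each clinic visit by a trained RA or nurse". Known SAEs go to the PI within 24 hours and to the IRB within 5 days. Trial 2, Overdose prevention, adds: "We will also assess any instances of OD and naloxone use at each visit". The list of changes to Trial 1 adds an overdose education module, so the same question may be asked there, although the Trial 1 text does not say so.
- **Leaving.** Withdrawal Procedures makes attendance and specimens a condition of receiving medication. Missed visits or missed specimens then lead to removal, and "if there is any evidence of nonadherence to the medication regimen, they will be withdrawn from the study". On pregnancy: "Should a subject become pregnant during the trial, her participation will be terminated". What follows is return of medication and device, and help with access to obstetric care.
- **Milder wording elsewhere.** Trial 2, Buprenorphine via computerized dispensing, says "any evidence of nonadherence may be grounds for discharge", and the matching Trial 1 section is also discretionary. Trial 1, Study Design, says "Participants in both groups will complete monthly follow-up assessments".
- **Efficacy data of early leavers.** Statistical methods in both trials: "Primary analyses will include all randomized subjects independent of early dropout and with missing urine specimens considered positive for illicit opioids".

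**The concern.** Both protocols justify IBT by the overdose and mortality risk of untreated opioid dependence, and their Purpose sections cite a 12-fold rise in premature death on waitlists. A participant discharged from IBT loses study buprenorphine and returns to that risk at the point where the described search for events stops. Abstinence has a rule for such people, because a missing urine is counted as positive. Deaths, overdoses, other SAEs and pregnancy outcomes have no such rule and cannot be filled in by assumption.

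At stake is the completeness of the SAE and overdose record, including the yearly IRB summary of SAE frequency and severity. With a target of 50 participants, one unrecorded death or overdose would change that record materially.

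**Working it through.** **1. Is there any other route by which an event after discharge would be found?**

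- Nightly IVR calls (Trial 1 and Trial 2, IVR daily monitoring) belong to the IBT package. They cover drug and alcohol use, craving and withdrawal symptoms; no adverse-event or overdose item is listed.
- The on-call phone depends on the participant calling in.
- The weekly staff review (Patient eligibility and status) covers active participants.
- The 24-hour and 5-day rules apply once an SAE is known. They set no cut-off date, but they do not find events.
- COVID-19 remote contact (both lists of changes) is for participants who are at high risk or have symptoms. It is not tracing of people who have left.
- Trial 2's cost window (Health economic evaluation) closes at discontinuation or trial completion, which fits a reading that discontinuation ends data collection.

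None of these provides active contact after exit.

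**2. The documents' figure on early exit.** Supporting preliminary data gives pilot 12-week retention of 92% (IBT) and 80% (WLC), 25 per arm, p=.42. Taking 23/25 against 20/25, a two-sided Fisher exact test gives p=0.417, which agrees.

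**3. Illustration of size for IBT.** Inputs: r = 0.92 at 12 weeks, and n = 25 per arm. The per-arm number is an assumption: it takes the revised target of 50 in Trial 1, Trial 2 aligned with it, and equal allocation. The exit rate is assumed constant to Week 24.

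- Weekly exit rate: λ = −ln(0.92)/12 = 0.00695.
- Out by Week 24: 1 − 0.92² = 0.1536; 25 × 0.1536 = 3.8 people.
- Mean weeks observed: 0.1536/0.00695 = 22.1 of 24.
- Person-weeks lost: about 47.4 of 25 × 24 = 600, or 7.9%.
- Monthly assessments missed: the sum over t = 4, 8, …, 24 of 25(1 − 0.92^(t/12)) is about 14 of 150.

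This counts every kind of exit. Discharge under the rule is only part of it.

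**4. WLC, for comparison.** The same steps with r = 0.80 give 1 − 0.80² = 36% out (9 of 25), 116 of 600 person-weeks (19.3%), and about 33 of 150 assessments missed. WLC makes up 116 of the 163 person-weeks lost in both arms (71%). That is ordinary non-attendance and should not be charged to the discharge rule.

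**The case against.** The strongest reply is that no sentence forbids contact after discharge. Assessments are set at fixed weeks (4, 8, 12, 16, 20 and 24) for both groups, with no exception for people off medication. The withdrawal paragraph opens with what is needed to receive medication, so it can be read as ending treatment only. Consent pages are not in the review copy and may allow later contact. The drug is approved for this use, and pilot adherence suggests few discharges. In Trial 2, evidence of drug use does not alter study procedures, so a positive urine should not trigger discharge.

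Much of this stands as a limit on certainty and size. It does not remove the point: the operative words are withdrawal from the study, and nothing states that a discharged participant stays in the monthly schedule. At best the protocols can be read two ways on a matter of participant safety.

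A reader might infer three stronger things that the documents do not support.

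- **That events go unsought equally in both arms because of this rule.** The attendance and nonadherence clauses are tied to receiving medication, which WLC participants do not get during their 24 weeks. A WLC participant who misses one month can still be asked about events at the next visit. Only the pregnancy clause names no arm.
- **That each missed assessment means four lost weeks.** After an intermittent miss, the events can be recovered at the next attended visit.
- **That a safety comparison is biased in a known direction.** No formal safety comparison is planned. Retained IBT participants are seen about weekly and WLC participants monthly, pilot exit was higher in WLC, and the discharge rule bears on IBT. The net direction is unknown.

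**Conclusion.** The point holds as a gap in safety follow-up after discharge. Followed as written, the Withdrawal Procedures of both trials end the only active search for harms that the protocols describe. This falls chiefly on IBT participants who have just lost buprenorphine. That later events are not sought is partly an inference from silence, supported by the explicit wording on withdrawal from the study.

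The number affected by the rule itself cannot be estimated from the documents and is probably small. The illustration of about 4 of 25 IBT participants and 47 of 600 person-weeks per trial rests on 25 per arm and on 12-week pilot retention continuing at a constant rate to Week 24. It includes exits for any reason. No planned test changes. The point merits a protocol change because the events concerned are serious and the remedy is light.

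**What to change.** Reword Withdrawal Procedures in both trials so that discharge or pregnancy ends study medication, not follow-up. Unless consent is withdrawn, keep these participants in the monthly assessments to Week 24. At minimum, have existing staff phone them at those times and record SAEs, overdose, death and pregnancy. Try the same call for WLC participants who miss an assessment. Report events over the same 24 weeks for all randomised participants, with the number contacted in each arm. Bring the discretionary discharge wording in the dispensing sections into line.

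**Cost.** Protocol and consent wording, and a modest number of calls. Under the assumptions above there would be about 14 missed assessments in IBT and 33 in WLC per trial, 47 together. Trial 2, Assessments, quotes 94% and 90% follow-up compliance, which would give 18 or 30 missed of 50 × 6 = 300. If visits are kept instead of calls, add the assessment payment, now $75.

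**Downsides.** Response will be incomplete, since people who stop attending are hard to reach. Phone contact carries a small confidentiality burden and needs consent wording consistent with the 42 CFR Part 2 protections that both protocols adopt. Calls alone leave the primary outcome as it is; a Week 24 visit would replace a urine counted as positive with an observed result.
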